### Sequence generation

The algorithm for the creation of the randomization list is the Maximal Procedure [53]. The Maximal Procedure is implemented in the R Package randomizeR [91]. Parameter for the Maximal Procedure are: Number of patients 34, Maximum Tolerated Imbalance (MTI) is set to 4 and Allocation ratio is 1:1.

This randomization is conducted twice: for adults and adolescents.

### Concealment mechanism

The randomization list for both groups generated by an external person working at the Center for Clinical Studies (CCS) of the University Hospital Erlangen is arranged into single tickets for each pseudonym for each study participant in the continuing order. The printed tickets are then put into opaque envelopes labelled with a consecutive randomization number. Then, the envelopes are taken to the Department of Orthodontics and Orofacial Orthopedics at the FAU Erlangen-Nürnberg and handed out to the lab manager. The study design is double-blind. Therefore, neither the clinical examiners nor the study participants will have knowledge about the randomization plan.

### Implementation

The company BioGaia will provide 6 closed storage boxes, containing 30 lozenges, for each of the 68 study participants in advance. Half of the canisters will contain test-lozenges (study group), the other half will be filled with control-lozenges (control group). Canisters are stored in a refrigerator in a save and lockable room at the Department of Orthodontics and Orofacial Orthopedics at FAU Erlangen-Nürnberg. Before the first appointment of an included study participant, the lab manager opens the envelope containing the assignment of the study participant to test or control group. After this process, the storage boxes will be labelled by the lab manager with the pseudonym of the study participant in accordance to the assignment in the envelope and the randomization plan generated by the CCS. The lab manager will hand over the storage canisters to the study leader before the first appointment, who will store them in a refrigerator. Each study participant will receive 6 closed storage canisters, containing 30 lozenges each, labelled with the pseudonym at the end of the regular consultation to ensure short transport times from the department to the private refrigerator in the home of the study participant. Therefore, study participants will receive five canisters. Half of them will receive lozenges containing probiotics, half of them will receive control-lozenges.

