Moreover, information about data protection and information material will be handed out to the patient and parents/legal guardians, including information about the study protocol, the appointments for collection of samples and measuring of clinical parameters and the investigation of clinical samples. Moreover, the benefits, risk and study cancellation criteria will be explained: Participants in the study group might have a benefit in the context of oral health since intake of probiotics was shown to reduce inflammation [45, 46]. The products of BioGaia containing *L. reuteri* were proven save in preterm babies, infants, children, healthy adults and immune compromised adults and no serious adverse effects have been observed up to the maximum tested dosage of 10 billion CFU per day, which equals 1000 times the recommended daily dose [57]. The recording of the clinical parameters, the collection of saliva samples and gingival crevicular fluid bears no risk for the study participants. Sampling of peripheral blood also poses no special risk for adults as it will be performed by licensed doctors except the usual risks of venous blood punctures, i.e. pain or hematoma/bruise at the puncture site and, in rare cases, thrombosis, local inflammation or permanent damage of blood vessels or nerves [58, 59]. Documents will be discussed with the patient and parents/legal guardians and questions will be answered ([name], [name], [name]). Signed data protection is mandatory prior to the beginning of the study. Moreover, age, sex and gender of study participants will be noted based on a medical history sheet. The documents will be collected by the study leader and stored in a save place together with the informed consent. Besides, the nature of orthodontic treatment, malocclusion as well as the current status of occlusion will be recorded for all study participants. In case that study participants received orthodontic treatment with lose or partly fixed appliances (e.g., due to impacted canines) before recruitment, this will also be written down. The entire information will be presented as study population characteristics and used for subgroup analyses.

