### Explanation for the choice of comparators

In this clinical trial, the influence of *L. reuteri* Prodentis®-lozenges (DSM 17938, ATCC PTA 5289) versus control lozenges on clinical parameters, the oral microbiota and the immune response during an orthodontic treatment in adolescent and adult patients will be compared. The active comparator *L. reuteri* Prodentis®-lozenges (DSM 17938, ATCC PTA 5289; BioGaia AB, Sweden) and the control comparator lozenges (BioGaia AB, Sweden) (Table 1) were chosen since the adjuvant use was proven beneficial concerning oral health [45, 46]. To our best knowledge, the effect of *L. reuteri* Prodentis®-lozenges, which contain two probiotic strains (DSM 17938, ATCC PTA 5289; BioGaia AB, Sweden), has not been studied during orthodontic treatment with fixed appliances so far. Since fixed appliances were shown to lead to strongest side effects shortly after insertion of appliance within the first three months [31, 32], we chose to start lozenge intake from the day of insertion of fixed appliance lasting for 12 weeks. The intake will be two times daily in accordance to the manufacturers’ instructions [60]. Lozenges consist of bulking agent (isomalt), *L. reuteri* DSM 17938 and *L. reuteri* ATCC PTA 5289, fully hydrogenated palm oil, peppermint flavor, menthol flavor, peppermint oil and sweetener (sucralose) [45, 60]. One lozenge consists of a minimum of 200 million live *L. reuteri* Prodentis [45, 60]. They are available under the name *L. reuteri* Prodentis®/™ (BioGaia AB, Sweden) [60]. Control-lozenges will be free of *L. reuteri* strains (Table 1).

**Table 1 Tab1:** List of comparators

Arms	Assigned interventions
Active Comparator: *Limosilactobacillus reuteri* Prodentis®-lozenges (BioGaia)	Dietary Supplement: *Limosilactobacillus reuteri* Prodentis®-lozenges (DSM 17938, ATCC PTA 5289) Two times per day for 12 weeks
Control Comparator: Control-lozenges (BioGaia)	Dietary Supplement: Control-lozenges (BioGaia) Two times per day for 12 weeks

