### Intervention description

Patients will receive lozenges and a protocol, in which they receive information about the intake and storage of lozenges:Supplementary intake of lozenges two times per day (1-0-1) for 12 weeks after the insertion of the fixed appliances (slowly melt on the tongue, mandatory after brushing of teeth)Storage of lozenges at in the refrigerator at 4 °CIntake protocol to control the regular intake of lozengesReturn of canisters for counting of left overs

Further, they receive an intake protocol, in which they should make a note about the daily intake of the lozenges. To control the lozenge intake, patients will be asked to return the used canisters for counting of left overs. Further, referring to adolescent study participants, not only the study participant (adolescent) but also the parent and/or legal guardian will be asked about the maintenance of perfect storage conditions during the study time (lozenge intake). Further, a nutrition protocol will be handed out to all participants to obtain an accurate, self-reported diet history on a daily basis. Participants should list their meals for breakfast, lunch and dinner as well as snacks. Additionally, the average water consumption and drinks containing sugar should be listed. Moreover, a special focus will be on the individual intake of milk products (e.g., yoghurt, cheese, milk), which should be noted in detail. Average consumption of milk products will be allowed.

Study participants in the test and control group will have five study time points (Fig. 2) including a base line check-up and four follow-up consultations during the study period for measurement of clinical parameters and taking of samples (Fig. 2). Sampling and examination according to the time line will be done during routine practice visits. The first consultation will be the base line check-up, where all clinical parameters and samples will be taken. Here, intake and nutrition protocol will be explained to the study participants and lozenges will be handed out to the patient. Day of insertion of fixed appliance is the start of the lozenge intake. There will be four follow-up consultations during the study period, where all clinical parameters and samples will be taken again for longitudinal evaluation. Taking of blood samples ([name]) will only be performed on T0, T2 and T3 and only in the adult group.

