**Fig. 2 Fig2:**
[figure not shown]
A time line showing all five study time points is given. Base line (T0) = before the insertion of the fixed appliance; T1 =  ~ one week (w) after insertion of fixed appliance/ start of lozenge intake; T2 =  ~ four w after insertion of fixed appliance/ start of lozenge intake; T3 =  ~ 12w after insertion of the fixed appliance = last day of lozenge intake; T4 =  ~ 24w after insertion of fixed appliance = 24w after start of lozenge intake = 12w after end of lozenge intake

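### The dispensing text gives both six and five canisters per participant, and the 1000-fold safety multiple does not follow from the dose stated for this trial (at most 25-fold)

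*Protocol article*

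**What the plan says.** **Regimen.** The intervention description in the protocol article sets out "Supplementary intake of lozenges two times per day (1-0-1) for 12 weeks after the insertion of the fixed appliances". The comparator table gives the same for both arms: "Two times per day for 12 weeks". The timeline figure's legend ties the end of intake to a visit: "T3 = ~ 12w after insertion of the fixed appliance = last day of lozenge intake".

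**Supply.** The Implementation section says that the manufacturer provides six boxes of 30 lozenges for every participant. It then says: "Each study participant will receive 6 closed storage canisters, containing 30 lozenges each". The sentence that follows reads: "Therefore, study participants will receive five canisters".

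**Adherence.** Under the intervention description, intake is checked in two ways: a daily intake record kept by the participant, and a count of the lozenges left in returned canisters. Statistical methods makes noncompliant intake a major protocol deviation, and Sample size applies the primary analysis to the per-protocol population.

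**Safety statement.** The recruitment and consent section lists what is to be explained to patients and guardians. On risk it says that no serious adverse effects were seen with the manufacturer's *L. reuteri* products up to a maximum tested dosage of "10 billion CFU per day, which equals 1000 times the recommended daily dose". On the trial product, the section on the choice of comparators says: "One lozenge consists of a minimum of 200 million live" bacteria. It adds that intake is twice daily, following the manufacturer's instructions.

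**The concern.** Two operative figures conflict with other figures in the same article.

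The first is the number of canisters. Six and five cannot both be what a participant receives, and only six covers the stated course. If five were handed out, a fully adherent participant would run out before T3, the visit defined as the last day of intake. The number issued is also the starting point for interpreting a return count, so the same number of returned lozenges would mean different adherence under the two figures.

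The second is the safety multiple. A patient or guardian who hears that the tested maximum is 1000 times the recommended dose will apply it to the lozenges being offered. The article's own content and frequency for those lozenges give a much smaller multiple. What is at stake is the accuracy of a risk statement, in a trial that includes minors.

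**Working it through.** **A. Canisters**

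Inputs: 2 lozenges a day for 12 weeks (intervention description, comparator table); 30 lozenges per canister, and 6 or 5 canisters (Implementation); primary endpoint at week 4 (Outcomes).

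- Lozenges needed = 2 × 7 × 12 = 168 over 84 days.
- Six canisters: 6 × 30 = 180; 180 / 2 = 90 days; 180 − 168 = 12 to spare.
- Five canisters: 5 × 30 = 150; 150 / 2 = 75 days; 168 − 150 = 18 short; 84 − 75 = 9 days uncovered; highest possible intake 150 / 168 = 89.3%.
- Needed by week 4: 2 × 28 = 56, covered by either number.

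Effect on the return count, for a participant who brings back 30 lozenges:

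- From six canisters: 180 − 30 = 150 taken; 150 / 168 = 89.3%.
- From five canisters: 150 − 30 = 120 taken; 120 / 168 = 71.4%.
- Difference: about 18 percentage points for the same count.

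A fully adherent participant returns 12 from six canisters. From five, an empty return still leaves the course 18 lozenges short.

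**B. Safety multiple**

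Inputs: tested maximum of 10 billion CFU per day and the stated multiple of 1000 (recruitment and consent section); at least 200 million per lozenge, twice daily (choice of comparators).

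- Recommended dose implied by the statement: 10,000 million / 1000 = 10 million CFU per day.
- Dose in this trial: 2 × 200 million = 400 million CFU per day at least.
- Multiple against the trial dose: 10,000 million / 400 million = 25. This is an upper bound, because 200 million is a minimum content.
- Gap between stated and derived multiple: 1000 / 25 = 40-fold.

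Other readings of the trial's figures:

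- One lozenge a day: 10,000 / 200 = 50.
- 200 million per strain, two strains, two lozenges a day: 10,000 / 800 = 12.5.
- For 1000 to hold against 400 million per day, the tested maximum would have to be 400 billion CFU per day. Alternatively, the recommended dose would have to be 10 million, one twentieth of a single lozenge.

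None of these readings of the trial's own figures comes near 1000.

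**The case against.** On the canisters, six appears twice and is enough for the course, while five appears once, after a connecting word that gives no reason for a different number. It reads as an editing slip. A reader might infer that participants will run out on day 75; the article does not support that, because the shortfall arises only if the lone figure is the one acted on. A reader might also infer that the primary endpoint is compromised. Exposure to week 4 is not, since 56 lozenges are available either way. The link to the per-protocol set is an inference too: the article names noncompliant intake as a major deviation without tying it to the canister count, and the daily intake record is a second check in which an exhausted supply should show as missed days. These points stand, and they limit the canister problem to T3, the last nine days of intake, and the reading of the return count.

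On the safety multiple, the sentence speaks of the manufacturer's *L. reuteri* products in general and rests on a cited source that is not at hand. Its recommended dose may belong to another product, in which case the sentence is unclear rather than miscalculated. That stands as a possibility. But no other product or dose is named, and the sentence sits in the explanation given for these lozenges. The consent documents are not shown, so it cannot be said that the figure has been put to participants in writing. Nor does anything here suggest that the trial dose is unsafe: 25 is only the ratio of two figures in the article.

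**Conclusion.** Both contradictions stand, in limited form.

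The Implementation section gives two canister numbers that differ by 30 lozenges. Six covers the 84 days with 12 to spare; five stops at day 75, 18 lozenges short, with a ceiling of 89% of planned intake. Five is probably a slip, and the week-4 endpoint is supplied under either number. If five were issued, T3 would fall after supply ends. Until the number is settled, the same return count can represent adherence levels about 18 percentage points apart. This assumes one lozenge per intake and a T3 visit at day 84.

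The 1000-fold multiple does not follow from the content and frequency stated for the trial lozenges, against which it is at most 25. That rests on taking the trial's own twice-daily intake as the recommended daily dose, as the article's reference to the manufacturer's instructions implies. Which canister number, reference dose or multiple is correct cannot be settled from the article.

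The corrections should be made, because one figure governs dispensing and adherence counting and the other is part of a risk explanation. Neither affects the design or the choice of endpoint.

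**What to change.** - Reconcile the canister statements to one number that agrees with the stated regimen and the definition of T3.
- Check the dispensing records for what each participant was actually given; Trial status shows that the study period has already begun for some. Use the number issued as the basis for the returned-lozenge count and, if it varied, apply it participant by participant.
- Restate the safety multiple against the dose taken in this trial, or name the product and daily dose to which the 1000-fold figure refers.
- Check whether the participant and guardian information carries the 1000-fold figure and, if it does, correct it.

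The cost is a change of wording in the protocol, possibly in the participant information, and a records check. If the multiple is restated against the trial dose, it becomes less favourable than the one now given. No change to sample size, endpoint or analysis method follows.

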### Who will be blinded and procedure for unblinding if needed

The study design is double blind. The storage boxes for the test and the control group will be identical and blinded. The study participants and examined raters will be blinded. Moreover, the whole clinic personnel will not have knowledge of the group affiliation of study participants. The only person having knowledge about the group affiliation will be the lab manager.

If unblinding is necessary due to any circumstances, e.g., the occurrence of AE, the lab manager will be informed to reveal the study participants allocation to the test or control group.

### Criteria for discontinuing or modifying allocated interventions

The exclusion criteria will not only be checked using a medical history sheet initially, but also measured and controlled regularly during the study period. If the study participant did not meet the exclusion criteria at base line, but does during the course of the study, the study participation will be canceled. All time points of analyses will be performed during routine practice visits to ensure adherence to the clinical trial. Therefore, slight variations of study time points will not lead to exclusion or discontinuation of the study. However, the exact study time point will be analysed as SD of the mean study time point and evaluated in the analyses and interpretation of the results. If the study participant decides to stop intake of lozenges due to any reason, the study participation will be terminated. The participation in the study is voluntary and a refusal to participate will not lead to disadvantages or changes in the orthodontic treatment. The withdrawal and cancellation of the study will be possible at any time during the study and will not lead to disadvantage or influence of the orthodontic treatment.

### Strategies to improve adherence to interventions and plans to promote participant retention and complete follow-up

All time points regarding the study procedure will be matched with routine practice visits. Thus, extra effort of the study participants can be minimized and the adherence to the clinical trial can be ensured. Study participants will receive a painted colorful intake and nutrition protocol as a motivational reminder, e.g., hung up on the refrigerator, in which the lozenges are stored. Since adolescents might not participate in the study, if taking of blood samples is mandatory, the taking of blood samples will only be performed in the adult group on 3 appointments. Adults with fear of needles, who would like to participate in the trial, will be enabled to participate without taking of blood samples (study design is then the same as for adolescents). If an adult seeks to participate in the study but is afraid of needles and/or injections, he will also be enabled to be part of the study. The aim of these strategies is to assure the achievement of the planned sample size within the scheduled time frame. Since orthodontic treatment with fixed appliances usually lasts for 18 to 24 months, all study participants will continue to show up to regular consultations in the Department of Orthodontics and Orofacial Orthopedics. Hence, a follow-up of study participants is given.

### Relevant concomitant care permitted or prohibited during the trial

Study participants do not receive any concomitant care permissions or prohibitions during the trial.

### Provisions for post-trial care

Study participants do not receive post-trial provisions. Since all study participants continue to have regular consultations in the department due to their ongoing orthodontic treatment with fixed appliances, which usually last 18 to 24 months, a follow-up of study participants is guarenteed.

### Plans for assessment and collection of outcomes

The clinical data assessment for this trial was standardized and trained in advance in a recent clinical study [52]. Collection of samples and clinical parameters will be performed by examined raters ([name], [name], [name]), who were trained in preliminary experiments to guarantee inter- and intra-examiner accuracy and a high data quality. Clinical parameters including the GI, PPD, MPI as well as the sulcus fluid flow rate (SFFR), which is measured during the appointment using the Periotron device, will be noted chair-side on a data sheet, which was designed in a previous study [52] and modified for this trial in advance. Immediately after collection of the clinical data on the data sheet, the data are transferred to a Microsoft Excel spreadsheet and stored in a secure folder with restricted access only to study staff.

### Data management and confidentiality

All participants of the study receive pseudonyms saved in a special program with restricted access only to the leader of the study ([name]). Patient data and collected data are processed according to the Guidelines of Data Protection set by the ‘Universitätsklinikum Erlangen and Friedrich-Alexander-Universität (FAU) Erlangen-Nürnberg' (Art. 6 Abs.2 Nr. 3 c BayDSG; data protection commissioner: [name]; [contact]).

### Plans for collection, laboratory evaluation and storage of biological specimens for genetic or molecular analysis in this trial/future use

After analyses, all samples will be disposed and destroyed properly.

### Statistical methods

Descriptive analysis is applied according to the scale of measurement of the variable: Nominal and ordinal variables are described by counts and percentages. Interval scaled variables are described by mean and standard deviation, or robust estimators like quantiles if necessary. The number of missing and valid values are counted for every variable. Inference statistics is based on a frequentist basis with hypothesis tests, p-values and confidence intervals. Applicable tests for this two-arm study are the t-test, WRT and Chi^2^-tests, according to the scale of measurement of the variable. The significance level is set to 5%; confidence intervals are two-sided with a length of 95%. Corrections for multiple testing may be applied, when a hypothesis is tested in multiple subgroups. The protocol presented in the paper is according to the SPIRIT guidelines [92, 93]. The size of the populations is reported by the Safety Evaluation Set (SES), Full analysis Set (FAS) and the Per Protocol Set (PPS). If these populations have remarkably different size, all endpoints and demographics are reported for each population. The software R will be used for data analysis. The following analysis sets will be defined for the statistical analysis of this study: (1) Safety Evaluation Set: The SES is the subset of all subjects who were exposed to any study intervention at least once; (2) Full Analysis Set: The FAS is the subset of subjects in the SES for whom the primary endpoint is available (here: all subjects who have GI data available at baseline and at four weeks); (3) Per Protocol Set: The PPS is the subset of subjects in the FAS without major protocol deviations. One major protocol deviation is the noncompliant intake of lozenge. Further major protocol deviations may be defined during the study.

An Interim analysis is not planned. Additional analyses will be performed to compare adolescents with adults. Subgroup analyses will be performed to compare study participants with inserted fixed full appliance in upper and lower arch versus inserted fixed full appliance in upper arch versus inserted fixed full appliance in lower arch. In case of missing data, e.g., the study participants missed one of the four follow-up consultations (T1-T4), the time point will not be evaluated for the study participant. For example, if the study participant misses T1, but show up to T2, the evaluation of the primary endpoint is possible for the study participant, however, longitudinal analyses is only possible after T2. Data will not be shared.

